### Statistical analysis

Patient demographics will be compared between the two groups to ensure that the data are balanced.

Intention-to-treat analysis will be used to analyze data including failed block. A per-protocol set will then be used to analyze data excluding the data for failed block. Continuous variables with a normal distribution will be reported as the means with the SD, which will be analyzed by an independent-samples *t* test. Data for the PAED and CHEOPS will be analyzed by either one-way repeated-measures ANOVA or Friedman’s repeated ANOVA on ranks according to the test for normality and homogeneity of variance. Categorical variables, such as the incidence of EA, will be reported as numbers and percentages, and analyzed by the chi-square test or Fisher’s exact test as appropriate. The reduction in pain, the decreased sevoflurane dose, and the dose of fentanyl in the PACU, regarded as covariates for the incidence of EA, will be assessed using logistic regression.

Statistical tests will be conducted using SPSS 12.0 (SPSS Inc., Chicago, IL, USA), and *P* < 0.05 will be considered statistically significant.

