## Background

Emergence agitation (EA) is a common phenomenon in the early postanesthetic period in children aged 3–9 years, which was first described by Eckenhoff et al. [1] in the early 1960s. The incidence of EA ranges from 10 to 80% [2, 3]. Although EA is short-lived, as it lasts an average of 30 min and is self-limiting [4], it may cause children to be prone to self-injury, interfere with a child’s recovery, increase healthcare costs, present a challenge to pediatric anesthesiologists, and decrease parents’ satisfaction with anesthesia [5–10]. Furthermore, EA is associated with postoperative maladaptive behavioral changes [11] and was recently considered a ‘vital sign’ [12]. Methods to prevent and treat EA have gained increased interest in pediatric anesthesia, but no gold standard method is currently available.

A variety of studies have investigated numerous contributors to EA, but the exact etiology of EA remains unclear. Inhalational agents with low blood solubility and pain are regarded as two significant predisposing factors of EA. The frequency of EA in children has increased due to the growing use of sevoflurane in general anesthesia, and nerve block administration can decrease the amount of sevoflurane used [13]. Pain plays an important role in EA [14–16], and adequate pain control can reduce the incidence of EA [6]. Numerous studies have reported that lumbar plexus block can provide superior analgesia effects that last 14.5 h [17]. Ultrasound technology has increased in popularity in pediatrics for lumbar plexus block because ultrasound guidance can provide direct visualization of the lumbar plexus to ensure both the safety and efficacy of lumbar plexus block [18–20]. However, controversies concerning the effect of nerve block on EA exist [13, 21–23], and trials studying lumbar plexus block on EA have not been performed.

We designed this prospective, randomized, and blinded study in children undergoing elective hip surgery and hypothesized that ultrasound-guided lumbar plexus block may decrease the incidence of EA in children undergoing elective hip surgery. This trial will provide clinical answers to verify our hypothesis and recommendations for clinical practice.

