### Data collection and management

Clinical characteristics include age, gender, weight, body mass index (BMI), ASA grade, duration of surgery, and duration of anesthesia (from induction of anesthesia to the discontinuation of sevoflurane).

Intraoperative data collection will include the following parameters: heart rate, noninvasive blood pressure, respiratory rate, dose of sevoflurane, and collective fentanyl dose.

Postoperative data collection will include the PAED score at every time point, incidence of EA, frequency of severe EA, duration of EA, time of emergence (from discontinuation of sevoflurane to the first response to a simple verbal command), extubation time (from the end of anesthesia to extubation), CHEOPS score at every time point, the incidence of complications and adverse events, and the dose of fentanyl in PACU.

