### Sample size estimation

The sample size was determined by a power analysis based on the incidence of EA in our previous pilot study. The incidence of EA of the control group in our pilot study was approximately 42%. We expect that the intervention group will exhibit a 15% reduced incidence of EA. Based on these assumptions, we found that 45 patients per group will provide a power of 80% for detecting differences in EA incidence at a significance level of 0.05. Considering a possible dropout rate of 10%, 50 patients will be included per group.

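### Comparing demographics cannot ensure balance; prespecifying age adjustment of the EA comparison would protect it better at almost no cost (minor)

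*Protocol article*

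**What the plan says.** The Statistical analysis section opens with the purpose of the baseline comparison: "Patient demographics will be compared between the two groups to ensure that the data are balanced". It names a t test for normally distributed continuous variables ("which will be analyzed by an independent-samples *t* test"), a chi-square or Fisher's exact test for categorical variables, and one general significance threshold of 0.05. It gives no separate criterion for balance.

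The primary outcome falls under the categorical rule: "Categorical variables, such as the incidence of EA, will be reported as numbers and percentages", followed by the chi-square or Fisher's exact test. The one logistic regression for EA takes pain reduction, sevoflurane dose and fentanyl dose in the recovery unit as covariates. All three arise after allocation, and no baseline covariate is named.

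Age is recorded for every child (Data collection and management: "Clinical characteristics include age, gender, weight, body mass index (BMI), ASA grade"). The Background describes EA as "a common phenomenon in the early postanesthetic period in children aged 3–9 years", while the Inclusion criteria admit ages 1 to 6, so that age band cuts through the trial population.

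**The concern.** The sentence gives a comparison a job it cannot do. Under valid randomisation the null hypothesis of a baseline test is true by design. A small P value therefore signals only chance, and a large one is not evidence of similarity. What can disturb the EA comparison is the difference actually realised in this trial, weighted by how strongly the variable predicts EA. The test does not measure that second part.

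At stake is a chance age difference that is judged acceptable and stays in the unadjusted EA comparison, where it could add to or mask part of a block effect. Adjusting for age in advance would deal with this and recover some precision. As written, the plan offers reassurance instead of protection.

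**Working it through.** **Plan's own figures.** The article gives no figure on baseline balance. The relevant inputs come from Sample size estimation: "45 patients per group will provide a power of 80% for detecting differences in EA incidence at a significance level of 0.05", then "Considering a possible dropout rate of 10%, 50 patients will be included per group". The dropout step reproduces: 45/0.9 = 50. The control EA rate is 42% and the expected reduction is 15%, read here as absolute (42% to 27%).

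**Step 1: what a 0.05 threshold would let through.** The largest observed difference that stays non-significant in a two-sided t test is t(0.975; 2n − 2) × √(2/n), in SD units.
- n = 50: 1.984 × 0.200 = 0.397 SD.
- n = 45: 1.987 × 0.211 = 0.419 SD.

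The article gives no SD for age. If ages are roughly uniform over the eligible range (assumed SD about 1.5 to 1.7 years), this is about 0.6 to 0.7 years.

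**Step 2: how often a sizeable difference passes.** At n = 50, a difference of 0.2 SD corresponds to t = 0.2/0.2 = 1.00. With 98 degrees of freedom, P(|t| > 1.00) = 0.320. Subtracting the 0.05 that is significant leaves 0.27. About 27% of randomisations would pass with an age difference above 0.2 SD.

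**Step 3: effect on the EA difference.** Model: logit P(EA) = a + b·x, where x is standardised age (uniform), b is the log odds ratio per SD, and a is set so that the average risk is 42%. The odds ratio is an assumption, shown as a range. The arms differ in mean age by 0.397 SD and there is no block effect.

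| Odds ratio per SD | Shift in EA difference | Share of 15 points |
|---|---|---|
| 1.5 | 3.8 points | 25% |
| 2.0 | 6.0 points | 40% |
| 2.5 | 7.4 points | 49% |

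**Step 4: error rate and power.** Same model, 50 per group, simulated, with the Pearson chi-square test. Values are for odds ratios 1.5, 2 and 2.5 in that order.
- Type I error, all trials: 5.4%, 5.3%, 5.2%.
- Type I error, all trials that pass the age test: 5.3%, 5.0%, 4.7%.
- Type I error, the 27% that pass with a difference above 0.2 SD: 5.7%, 6.5%, 6.9%. Repeat runs agree on about 6 to 7%.
- Power for 42% against 27%: about 35% unadjusted, and about 36%, 38% and 40% with age in a logistic model.

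The 35% is far below the 80% the article states, because 42% against 27% needs 157 per group. That is a separate problem, and this point does not depend on it.

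**The case against.** The strongest reply is that an unadjusted 2×2 test is a legitimate primary analysis of a randomised trial. Step 4 supports this: the error rate is close to 5% over all trials, and also over all trials that pass the check. A reader might infer that the primary test is invalid, or that passing the check causes bias. The documents and the figures support neither.

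The balance rule is also inferred. The article says only that demographics will be compared. It does not say that P above 0.05 means balanced, and the chi-square or Fisher test is planned whatever the comparison shows. The check gates nothing.

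The age effect is assumed, and the range is generous. A uniform distribution spans 2√3 = 3.46 SD, so odds ratios of 1.5 to 2.5 per SD imply roughly 4-fold (1.5^3.46) to 24-fold (2.5^3.46) odds between the youngest and oldest children. The Background names an age band but gives no gradient. Step 3 also uses the largest difference that can pass. The median absolute difference is about 0.14 SD, and only about 3% of trials pass with one above 0.35 SD.

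Finally, the article does not mention stratified allocation by age, but such detail may stand in the full protocol, so nothing is made of that silence.

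All of this limits the size of the point. It does not rescue the stated purpose of the comparison, nor does it make the three post-randomisation covariates a substitute for a baseline one.

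**Conclusion.** The point holds as a minor one. The claim to ensure balance by comparing demographics is wrong as stated, and the planned EA analyses leave unused a baseline variable that the article itself links to EA. What is lost is some precision and protection against a chance age imbalance. Under an assumed odds ratio of 1.5 to 2.5 per SD, the shift is about 4 to 7.5 points at the largest imbalance that would pass, type I error is about 6 to 7% in roughly a quarter of trials, and power is lower by about 1 to 5 points. If age matters less than assumed, all of these shrink.

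Two stronger readings should not be drawn. A reader might compute the power of a t test for a true half-SD age difference and infer that such an imbalance would often go unnoticed. That calculation concerns a difference between populations, which is zero under randomisation. A realised half-SD difference gives t = 0.5 × √(n/2) = 2.50 (P = 0.014) at 50 per group, or 2.37 (P = 0.020) at 45, so the t test would flag it. A reader might also multiply the 5% false-alarm rate across the listed baseline variables as if they were independent. Age and weight are plainly correlated in children of 1 to 6 years, so that figure would be overstated.

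**What to change.** Replace the opening sentence of Statistical analysis with text to this effect: *Baseline characteristics (age, gender, weight, BMI, ASA grade) will be summarised by group without significance tests. The primary intention-to-treat comparison of EA incidence will be adjusted for age (continuous) by logistic regression, whatever the observed balance, and reported as an age-standardised risk difference with 95% confidence interval. The unadjusted chi-square or Fisher's exact result will be reported as supportive.*

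The covariate must be fixed before the group codes are opened. If that moment has passed, the age-adjusted result should be labelled as not prespecified and reported beside the planned test.

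The cost is a change of wording and one model term. Age is already collected, and no extra children or procedures are needed. The small downside is that the primary estimate comes from a model instead of directly from a 2×2 table.

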**Methods/design:**

We designed a prospective, randomized, controlled, blinded trial to determine the effect of ultrasound-guided lumbar plexus block on EA. A total of 100 American Society of Anesthesiologists class I–II children (1–6 years old) scheduled for elective hip surgery will be recruited for this study. Participants will be randomized at a 1:1 ratio to receive either ultrasound-guided lumbar plexus block or fentanyl after the induction of general anesthesia. The primary outcome is the incidence of EA 30 min after emergence from anesthesia using the Pediatric Anesthesia Emergence Delirium (PAED) score. The secondary outcomes are the severity and duration of EA 30 min after emergence from anesthesia using the PAED score, postoperative pain evaluated by the Children’s Hospital of Eastern Ontario Pain Scale, and the incidence of postoperative adverse events. Randomization will be conducted using a computer-generated randomization schedule. Outcome assessors and data collectors will be blinded to the group allocations. Assessments will be performed before surgery, intraoperatively, and postoperatively at every time point.

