#### Secondary objectives

The secondary objectives are as follows:to compare the severity and duration of EA between the ultrasound-guided lumbar block group and the control group;to compare postoperative pain between the two groups; andto compare the occurrence of postoperative complications between the two groups.

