### Intraoperative anesthetic management and postoperative assessment

If the heart rate is reduced to less than 50 beats per min during the operation, then 10 μg/kg atropine will be used. If the blood pressure is reduced by greater than 25% of the baseline value, then 0.1 mg/kg ephedrine will be administered. At the end of surgery, sevoflurane will be discontinued, and the fresh gas flow will be increased to 6 l/min.

After completion of the operation, children will be transferred to the PACU and observed until the end of the study period. ECG results, noninvasive blood pressure, and pulse oximetry will also be measured every 5 min. After recovery of adequate of spontaneous breathing, purposeful movement, and eye opening, the endotracheal tube will be removed.

EA will be assessed using the PAED scale (Table 1) [24] at 0, 5, 10, 20, and 30 min after emergence from anesthesia. The PAED score will be documented by the same well-trained doctor, who will be blinded to the allocation group. The PAED score consists of five psychometric items: eye contact with the caregiver, purposeful action, awareness of surroundings, restlessness, and inconsolability. Each item is scored on a 5-point scale (0–4). The maximum score is 20. EA is defined as a PAED score greater than 10 points [25]. Patients with severe EA (PAED score ≥ 13) [24] will be treated with a bolus of 0.5 μg/kg fentanyl. The incidence of EA, frequency of severe EA, and duration of EA will be documented.

**Table 1 Tab1:** Pediatric Anesthesia Emergence Delirium (PAED) scale

1. The child makes eye contact with the caregiver	
2. The child’s actions are purposeful	
3. The child is aware of his/her surroundings	
4. The child is restless	
5. The child is inconsolable	

Items 1, 2, and 3 are reverse scored as follows: 4 = not at all, 3 = just a little, 2 = quite a bit, 1 = very much, 0 = extremely

Items 4 and 5 are scored as follows: 0 = not at all, 1 = just a little, 2 = quite a bit, 3 = very much, 4 = extremely

Scores for each item are summed to obtain a total PAED score between 0 and 20

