Postoperative pain will be evaluated using the CHEOPS by a blinded observer at 0, 5, 10, 20, and 30 min after emergence from anesthesia in the PACU. The CHEOPS is a pain-scoring method applied for children aged 1–7 years. The scale was established by McGrath et al. [26]. The CHEOPS consists of six items: crying, facial expression, verbalization, torso position, touching of the affected area, and leg movement. The maximum score is 13, and the minimum score is 4 points. Children with CHEOPS score ≥ 4 will be treated with a bolus of 0.5 μg/kg fentanyl.

Hemodynamic changes and complications will be recorded in the PACU and compared between the two groups.

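### The repeated PAED and CHEOPS scores are assigned to tests of change over time that, as named, contain no group term, so they do not deliver the between-arm secondary comparisons

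*Protocol article*

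**What the plan says.** The trial has two parallel arms: "Participants will be randomized at a 1:1 ratio" (Abstract, Methods/design). Under Secondary objectives, two aims concern the scores: "to compare the severity and duration of EA between the ultrasound-guided lumbar block group and the control group", and "to compare postoperative pain between the two groups". Secondary outcomes names PAED as the measure for the first and CHEOPS for the second.

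Both scales are scored five times in each child. PAED is taken "at 0, 5, 10, 20, and 30 min after emergence from anesthesia. The PAED score will be documented", and CHEOPS "at 0, 5, 10, 20, and 30 min after emergence from anesthesia in the PACU" (Intraoperative anesthetic management and postoperative assessment).

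The Statistical analysis section gives these scores their own sentence: "Data for the PAED and CHEOPS will be analyzed by either one-way repeated-measures ANOVA or" Friedman's test on ranks, with the choice made "according to the test for normality and homogeneity of variance". It mentions no group factor and no group-by-time term for them. The same section assigns the independent-samples t test to normally distributed continuous variables and the chi-square or Fisher test to categorical variables such as EA incidence. It names no rank test between arms.

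**The concern.** The objectives ask whether the arms differ. The named tests ask whether scores change over the first 30 minutes. A one-way repeated-measures ANOVA has a single within-child factor, here time. Friedman's test ranks each child's five scores against each other, so the level at which a child scores drops out.

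Two errors could follow if the plan is applied literally. A real and steady benefit of the block on pain or agitation scores would go untested. And a small p-value produced by ordinary recovery could be reported as evidence about the block. Pain matters here beyond its place in the list of outcomes, because the Background presents pain relief as a route by which the block might reduce EA.

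**Working it through.** The plan states no figure for this point, so there is none to reproduce. The check has an algebraic part, which needs no assumptions, and a simulation, which does.

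**1. Algebra.** Let Y_ij be the score of child i at time j, with n children and t = 5 times. The one-way repeated-measures statistic is

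F = [n Σ_j (Ȳ_.j − Ȳ_..)² / (t − 1)] / [Σ_ij (Y_ij − Ȳ_i. − Ȳ_.j + Ȳ_..)² / ((t − 1)(n − 1))].

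Subtract a constant δ from every score in one arm, where that arm is half of the children:

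- Each time mean Ȳ_.j and the grand mean Ȳ_.. fall by δ/2, so Ȳ_.j − Ȳ_.. is unchanged.
- In the shifted arm, the residual changes by −δ + δ + δ/2 − δ/2 = 0.
- In the other arm, it changes by 0 − 0 + δ/2 − δ/2 = 0.

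F is therefore unchanged. Friedman's statistic is unchanged because the ranks within each child are unchanged. The identity assumes that every score can move by δ. PAED runs from 0 to 20 and CHEOPS from 4 to 13, so scores near the floor would be truncated or tied and invariance would then be only approximate.

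**2. Numerical check of the identity.** In one simulated data set (45 + 45 children, 5 times, unbounded normal scores), one arm was lowered by 0, 3 and 8 points.

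| Shift | One-way RM ANOVA p | Friedman p | Between-arm p (t test on child means) |
|---|---|---|---|
| 0 | 0.525 | 0.839 | 0.85 |
| 3 | 0.525 | 0.839 | 2.0 × 10⁻²⁶ |
| 8 | 0.525 | 0.839 | 4.3 × 10⁻⁵⁹ |

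**3. Rejection rates.** Inputs from the protocol are 45 analysable children per arm and a significance level of 0.05 (Sample size estimation), and five assessments. The protocol gives no SD. A between-child SD of 2 and a residual SD of 2 are assumed. There were 2,000 runs.

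| Scenario | Pooled one-way RM ANOVA | Pooled Friedman | Group main effect |
|---|---|---|---|
| Constant 3-point arm difference, no time trend | 5.1% | 5.2% | 100% |
| No arm difference, 1-point fall per assessment | 100% | 100% | 4.0% |
| Neither | 5.0% | 4.8% | 4.9% |

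The 100% for the group effect depends on the assumed SDs. The variance of a child's mean is 2² + 2²/5 = 4.8. The standard error of the arm difference is √(2 × 4.8/45) = 0.46, so 3 points is about 6.5 standard errors. With both SDs doubled to 4, the variance is 19.2, the standard error is 0.92 and the ratio is about 3.2, which gives power of about 90%. The insensitivity of the two named tests does not depend on the SDs.

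**4. Running the tests in each arm separately.** In the control arm alone, the two tests rejected in 4.5% and 4.7% of runs in the first scenario and in 100% in the second. Two separate tests of time do not compare the arms, even if one is significant and the other is not.

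**The case against.** The best defence is that the ANOVA is loosely named. Homogeneity of variance is ordinarily checked between groups, whereas a purely within-child ANOVA usually raises the question of sphericity. Read with the secondary objectives, the sentence may mean a repeated-measures ANOVA with group as its one between-child factor. That reading is plausible for the ANOVA. It does not rescue Friedman's test, which has no between-subject factor, and no between-arm rank test is named elsewhere. If the scores fail the normality check, they have no stated arm comparison.

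A second defence is that an unseen analysis plan may settle this. But the article is not silent: it names methods, and they do not match its objectives.

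A third is that other tests cover the same ground. This is partly right and limits the point. Frequency of severe EA is categorical and falls under chi-square or Fisher. Duration of EA, if normally distributed, falls under the t test. A reader might infer that EA severity is not compared between arms at all, but the documents do not support that. For CHEOPS there is no such second route: the logistic regression uses pain reduction as a covariate for EA and does not compare pain between arms.

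A reader might also infer that power for an arm difference equals the type I error. That holds only without a time trend. With a trend, rejection can approach 100% whatever the block does. The accurate statement is that the result does not depend on a constant arm difference.

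**Conclusion.** The point stands, limited to the repeated PAED and CHEOPS score analyses. As named, both methods test change over time within child and do not provide the between-arm comparisons set as secondary objectives. CHEOPS pain intensity is the most exposed, because it has no other stated analysis.

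The insensitivity to a constant arm difference is algebraic, subject to the floor effects of the bounded scales. The rejection rates illustrate it under assumed SDs and effects and are not estimates for this trial. That the tests would be significant regardless of the block rests on scores falling during recovery, which is likely but not stated in the protocol.

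Nothing here touches the primary outcome. EA incidence has a valid between-arm test, and the sample size is based on it. A reader might infer that the trial's main conclusion is at risk, but this sentence of the plan gives no ground for that. The matter should be fixed, but it does not invalidate the trial.

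**What to change.** Replace the sentence with one prespecified between-arm analysis for each score: a repeated-measures model with group, time and group-by-time and within-child correlation across the five assessments, reporting the between-arm mean difference with its 95% confidence interval.

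Replace Friedman's test with one rank-based between-arm sensitivity analysis that is always reported and not triggered by a normality test. An example is a rank-sum test with the Hodges–Lehmann difference on each child's peak score over 0–30 min. State the summary measure in advance. Because fentanyl given in the PACU can affect later scores under any of these analyses, say that the comparison is of scores with that treatment as given.

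All the data are already collected. The cost is slightly more analysis work and a dated change before unblinding. The date matters because Study time reports completion in October 2018, while Trial status says that recruitment continues.

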### Randomization

Randomization will be based on computer-generated allocation, and random numbers will be concealed in opaque envelopes. After intubation, the envelope corresponding to a number in the randomization table will be opened, and the participant will be randomly assigned to either the ultrasound-guided lumbar block group or the control group at a 1:1 allocation ratio according to random number.

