The operation will be performed at least 15 min after the nerve block. During the operation, anesthesia will be maintained with 60% nitrous oxide, 40% oxygen, and 2% end-tidal sevoflurane. If the increases in heart rate, noninvasive blood pressure, and respiratory rate are greater than 15% from the baseline the values during the operation, the concentration of sevoflurane will be increased by 0.5%. Conversely, if the reductions in heart rate, noninvasive blood pressure, and respiratory rate are greater than 15% of the baseline values during the operation, the concentration of sevoflurane will be reduced by 0.5% [23]. If additional fentanyl is required when the heart rate, blood pressure, and respiratory rate increase by greater than 25% intraoperatively, the patient will be recorded as a failure or an inadequate lumbar plexus block and also be followed up. Immediate complications will be recorded and treated.

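### The logistic regression for EA uses three post-randomisation covariates, so it cannot give a valid block effect, and its PACU fentanyl term is partly reverse-causal; the ITT comparison is unaffected

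*Protocol article*

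**What the plan says.** The Statistical analysis section of the protocol article compares the incidence of EA between arms by chi-square or Fisher's exact test, under intention-to-treat and then per protocol. It then adds a logistic regression: "The reduction in pain, the decreased sevoflurane dose, and the dose of fentanyl in the PACU, regarded as covariates for the incidence of EA". It does not say whether treatment group is a term in that model, what question the model answers, or how it ranks against the chi-square or Fisher result. It does not call the model exploratory or a mediation analysis.

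Other sections fix the order of events:

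- **Randomization:** "After intubation, the envelope corresponding to a number in the randomization table will be opened".
- **Background:** "nerve block administration can decrease the amount of sevoflurane used"; "lumbar plexus block can provide superior analgesia effects"; "adequate pain control can reduce the incidence of EA".
- **Ultrasound-guided lumbar plexus block group** (the Control group section has the same rule): when vital signs rise by more than 15% from baseline, "the concentration of sevoflurane will be increased by 0.5" per cent, with a matching reduction when they fall.
- **Intraoperative anesthetic management and postoperative assessment:** EA is a PAED score above 10. "Patients with severe EA (PAED score ≥ 13) [24] will be treated with a bolus" of fentanyl. A CHEOPS score of 4 or more triggers the same fentanyl bolus, and the scale's stated minimum is 4.

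**The concern.** A covariate in a model for a randomised treatment effect should be fixed before allocation. A variable that the treatment changes on its way to the outcome absorbs part of the effect when it is held constant. A variable that the outcome changes brings the outcome in on the predictor side. This plan has both kinds.

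What is at stake is interpretation. This is the only multivariable model the article names for the primary outcome. A significant crude difference could sit beside a null block coefficient and be reported as no independent effect of the block, although the block had worked exactly as the Background proposes. PACU fentanyl could likewise be reported as a risk factor for EA when agitation was a reason for giving it.

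**Working it through.** **Step 1: timing.** Allocation is revealed after intubation. Sevoflurane is titrated during surgery, pain is scored in the PACU, and PACU fentanyl is given there. All three covariates therefore follow allocation.

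**Step 2: role of each variable, from the document's own statements.**

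| Covariate | Affected by | Role |
|---|---|---|
| Pain reduction | The block (Background); also a secondary outcome | Mediator |
| Decreased sevoflurane dose | The block (Background); titrated to response after allocation | Mediator |
| PACU fentanyl dose | Severe EA (PAED 13 or more) and pain (CHEOPS 4 or more) | Partly a consequence of EA, partly of a mediator |

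Severe EA starts at 13 and EA starts above 10, so every child treated for severe EA is already an EA case.

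**Step 3: size.** The plan gives no figure for this model, so there is none to reproduce. The anchors are a control EA rate of 42% (Sample size estimation) and the expected 15% reduction, taken here as 15 percentage points: 42% − 15% = 27%. The true odds ratio (OR) is then (0.27/0.73) / (0.42/0.58) = 0.370 / 0.724 = 0.51.

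The article gives no path strengths. Those assumed were:

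- pain = −0.8 × block + noise (SD 1)
- sevoflurane = −0.5 × block + noise (SD 1)
- logit P(EA) = a + b × [−d × block + m × (0.9 × pain + 0.4 × sevoflurane)], with a and b set to give 42% and 27%
- PACU fentanyl = one unit for high pain, plus one unit in 60% of EA cases

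Full mediation is d = 0, m = 1. Half mediation is d = m = 0.5: the direct part is −0.50 and the mediated part is 0.5 × (0.9 × −0.8 + 0.4 × −0.5) = −0.46, both before scaling by b. In two scenarios an unmeasured variable raises both pain and EA. ORs come from 200,000 children per arm. Power is the share of 1,000 simulated trials of 50 per arm that are significant in favour of the block.

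| Scenario | OR, block only | OR, + pain and sevoflurane | OR, all three | OR, fentanyl only | Power, block only | Power, all three |
|---|---|---|---|---|---|---|
| Half mediated | 0.51 | 0.70 | 0.71 | 0.86 | 32% | 10% |
| Fully mediated | 0.51 | 0.99 | 1.01 | 0.90 | 36% | 3% |
| Half mediated, common cause | 0.51 | 0.92 | 0.92 | 0.86 | 34% | 4% |
| Fully mediated, common cause | 0.51 | 1.38 | 1.40 | 0.91 | 36% | 1% |

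**Step 4: sensitivity of the fentanyl term.** In a simpler model with pain as the only path and a yes/no fentanyl indicator, raising the pain cut-off for fentanyl through 0, 0.5, 1, 1.5 and 2 SD gave fentanyl-adjusted block ORs of about 1.00, 0.93, 0.75, 0.61 and 0.54. No single figure for this term can be defended. Taken literally, the stated trigger makes every child eligible, because the lowest possible CHEOPS score already meets it. What the dose would measure is therefore unclear.

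**The case against.** **The primary comparison is sound.** EA incidence is compared by an unadjusted randomised test under intention-to-treat, and that test answers the primary objective. The regression is one later sentence and is not called confirmatory. This stands. A reader might infer that the trial's main result would be lost; the document does not support that, because the flaw is confined to the regression.

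**Treatment group is not named in the model.** The sentence can be read as asking which factors go with EA, in which case no block effect is estimated and none can be erased. This stands in part. The word covariates points to a model with treatment in it, but that is an inference. Without treatment, the fentanyl term is still partly reverse-causal.

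**The simulated sizes depend on the assumptions.** This stands. Under full mediation with no common cause, an OR near 1 is built in. With half mediation and no common cause the effect is weakened, not erased. A reader might also infer that PACU fentanyl is bound to appear as a strong risk factor. That is not established, because pain triggers it too and the stated pain trigger covers every child.

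**Lack of baseline adjustment.** A reader might count it as an error that no baseline variable is named for the model. It is not: an unadjusted randomised comparison is valid, and an analysis plan that is not shown may add such variables.

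**Conclusion.** The regression is wrong as written, but the consequence is limited. With treatment in the model, its coefficient is not the effect of the block on EA and may be weakened, erased or reversed: from a true OR of 0.51 to 0.71, about 1.0 or 1.40 in the cases above. These figures are illustrations. They rest on assumed path strengths and on reading the expected reduction as 15 points, and they are not predictions for this trial. With treatment absent, the model shows associations only, and its fentanyl term should not be read as a risk factor. The causal order itself needs no assumption beyond the article's own account of the mechanism and its treatment triggers. The intention-to-treat comparison stands. This should be corrected before analysis, but it does not threaten the primary result.

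**What to change.** Change the Statistical analysis text as follows:

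1. State that the ITT comparison of EA proportions, reported as a risk difference with a 95% confidence interval, is the sole basis for the conclusion about the block.
2. Remove PACU fentanyl as a predictor of EA and compare it between arms as an outcome.
3. Compare pain and sevoflurane dose between arms as outcomes. Label any EA model that contains them as exploratory mediation, not as an adjusted treatment effect.
4. Optionally, if an adjusted treatment effect is wanted, use only pre-randomisation variables already collected, such as age, weight and ASA grade. Durations of surgery and anaesthesia appear in the same list of clinical characteristics but arise after allocation, so they do not qualify.
5. Reconcile the CHEOPS minimum of 4 with the treatment trigger of 4 or more, because together they determine what the PACU fentanyl dose measures.

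Items 1 to 4 change wording only; every variable is already in the data collection list. The cost is that the secondary model no longer supports statements about independent predictors of EA.
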